## Abstract

**Background:**

Breastfeeding mothers’ decisions to donate their milk is influenced by their knowledge, attitudes, and subjective norms such as their family’s opinions on milk donation. In Iran, women have favorable knowledge and positive attitudes toward breastfeeding, but they lack sufficient information and education about milk banks. With respect to current childbearing policies, an increase in the number of infants who will be admitted to neonatal intensive care units is expected. Accordingly, improving milk donation behavior, which requires mothers’ intention and ability to donate breast milk, is important for infants’ survival and well-being. Therefore, this study aims to evaluate whether an educational program based on the theory of planned behavior affects breastfeeding mothers’ decisions to donate their breast milk.

**Methods:**

This cluster randomized controlled trial will be conducted in health centers affiliated to Tehran University of Medical Sciences and will enroll 66 breastfeeding mothers (intervention, *n* = 33; control, *n* = 33). After collecting baseline data, the intervention group will begin receiving a 60-minute weekly educational program based on Theory of Planned Behavior components for four weeks. The first follow-up assessment will be conducted immediately after the intervention, and the final one will be conducted 12 weeks later. The primary outcomes are the number of mothers who have donated their breast milk and changes in breastfeeding mothers’ knowledge, attitude, subjective norms, and perceived behavioral control about donor human milk and intention to donate milk.

**Discussion:**

This trial will evaluate if a well-designed educational program can improve breastfeeding mothers’ knowledge and promote their behavioral factors regarding milk donation and lead to a significant increase in the number of potential milk donors.

**Trial registration:**

irct.ir (IRCT20230124057203N1) registered February 14, 2023.

## Background

Exclusive breastfeeding for about the first six months and continued breastfeeding with complementary foods up to two years or more are needed to ensure optimal growth for all infants [1]. Infant feeding practices can consist of breast milk, formula feeding, and supplementary feeding [2–4]. Among these options, mother’s own milk (MOM) is uniquely designed for infants and has many health benefits for both mother and baby [5]. However, if the MOM is not available for any reason, donor human milk (DHM) available in human milk banks (HMBs) is the best option [6]. All over the world, there are more than 750 HMBs, and according to the latest updates, a total of 12 HMBs have been established in Iran [7]. The first HMB in Iran was established in 2016 at Al-Zahra teaching hospital in Tabriz, and currently, two hospitals have HMBs in Tehran (the capital of Iran) [7, 8]. One of the most important challenges for HMBs is increasing the number of donors in order to meet growing needs for donor milk because increasing donation allows more infants, who would be otherwise unable to do so, to take advantage of human milk [9].

Women’s decisions to donate their milk is influenced by their knowledge, attitude and subjective norms like their husband’s opinions [10, 11]. A descriptive study of the experiences of women who donated their milk to a HMB showed that donors had strong positive attitudes toward breastfeeding, and 96% of them felt that they were knowledgable about milk donation. Besides, participants reported that they felt supported by their husband, family and friends in different ways, and none of them reported feeling unsupported. In this study women described their confidence and ability to donate their milk which indicate the role of control beliefs in their milk donation experience [12].

In 2019, the Human Milk Banking Association of North America reported that nearly 7.4 million ounces of pasteurized human milk were donated by 12,491 breastfeeding mothers representing a nearly one million ounce increase over the number of ounces donated in 2018 [13]. In Iran in 2020, it was reported that 7,270 ounces of human milk were donated by 81 mothers, and in 2021, 28,167 ounces of human milk were donated by 51 mothers in the Omolbanin HMB (the fourth HMB in Iran) [14]. Considering that the average age of marriage in Iran has increased and the government is prioritizing childbearing policies, there are many mothers who become pregnant at advanced ages, and these mothers are at a higher risk of experiencing pregnancy complications that can result in premature birth [15]. Therefore, it is expected that the number of infants who are admitted to neonatal intensive care units will increase and, increasing the number of milk banks and improving attitudes toward milk donation is crucial in ensuring the survival and well-being of these infants.

Reviewing the literature on milk donation behavior has revealed that mothers often do not have enough knowledge about milk donation and HMBs, and especially in Iran, despite the favorable knowledge and positive attitudes of women toward breastfeeding, the availability of information and education about milk bank to mothers is very limited. Therefore, there is a need for educational interventions by health professionals to increase mothers’ knowledge and promote factors that influence milk donation behavior, and to encourage potential donors to donate their breast milk to HMBs [10–12, 16, 17].

Meanwhile, in regard to breastfeeding and milk donation, it seems that behavioral theory-based educational interventions have the ability to provide a useful framework to give essential information to mothers and improve their understanding on this subject [12, 18]. One such behavioral theory is the theory of planned behavior (TPB), which is commonly used to understand how human behavior works [19]. Since milk donation is a voluntary behavior that requires the mothers’ intention and ability to donate their breast milk, the most matching theory to this behavior and this study’s objectives is TPB. Thus, this study seeks to assess whether the educational program based on theory of planned behavior (TPB) influences breastfeeding mothers’ decision to donate their breast milk.

### Hypothesis

An educational intervention based on TPB on breastfeeding mothers will produce changes in knowledge, attitude, subjective norms, perceived behavioral control, and intention of donating breast milk which in turn will modify behavior, thus resulting in increased breast milk donation to HMBs.

### Objectives

The main objective of this study is to assess the effectiveness of an educational intervention based on TPB in breastfeeding mothers on donating breast milk to HMBs.

Secondary objectives of the study are:

To evaluate changes in breastfeeding mothers’ knowledge about milk donation.To evaluate the effect of the educational program on behavioral determinants (attitude, subjective norms, perceived behavioral control and behavioral intention).To analyze the association of behavioral determinants with milk donation.To study the relationship between social demographic variables and milk donation.

## Methods

### Study design

A cluster randomized controlled trial will be carried out on breastfeeding mothers referred to health centers affiliated to Tehran University of Medical Sciences. A cluster randomized controlled trial design was chosen because it makes it easier for mothers to attend classes at their local health center, and in this design, the phenomenon of contamination between the intervention and control groups is avoided. Besides, it can help us increase the representativeness and generalizability of our study population and results. The control group allows us to analyze the direct effect of the intervention and discount an increase in milk donation due to other factors [20]. This study was approved by the Research Ethics Committees of School of Nursing and Midwifery & Rehabilitation - Tehran University of Medical Sciences (IR.TUMS.FNM.REC.1401.150).

### Setting

This study will be conducted in health centers affiliated to Tehran University of Medical Sciences. Tehran University of Medical Sciences covers primary health care services of 5 out of 22 districts of Tehran City (district numbers 10, 11, 16, 17 and 19) [21]. These health centers were chosen because they cover a significant portion of breastfeeding mothers of South Tehran, who usually bring their infants to theses\ health centers for vaccination, screening or growth monitoring. However, we will include four of these districts in our study (district numbers 10, 11, 16 and 17) because the health centers of district number 19 do not have the equipment for holding in-person classes and the population of Iranian breastfeeding mothers in that district is limited. These four districts have a total of 20 health centers. From among all these health centers, we will choose eight centers using simple randomization method; then, a cluster of four centers will be randomly selected for collecting the intervention group and four centers for collecting the control group. We will recruit eight to nine participants from each health center.

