### Sample size

In order to provide a power of 95% with 95% confidence interval the following formula and the standard deviation of 3.17 to 3.21 (according to the same study’s findings) will be used [18]. The sample size was estimated at 30, and then allowing for 10% attrition, we plan to recruit 33 samples per group and a total of 66 study participants.$$ n=\frac{{\left({z}_{1-\frac{\alpha }{2}}+{z}_{1-\beta }\right)}^{2}\left({s}_{1}^{2}+{s}_{2}^{2}\right)}{{\left({\overline{x}}_{1}-{\overline{x}}_{2}\right)}^{2}}$$$$ \frac{{\left(1.96+1.64\right)}^{2}\left({3.21}^{2}+{3.17}^{2}\right)}{{3}^{2}}=29.4\cong 30$$$$ 30+30\left(0.1\right)=33$$

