Lectures, small groups discussion, educational pamphlets and booklet, PowerPoint presentations, showing videos and pictures, will be the main educational methods and materials that we are going to use in order to make the program effective and interesting. Moreover, we will ask mothers to share the booklet and pamphlets with their family and friends. Sessions will be held in health centers for the intervention group while the control group will receive only usual education.

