### Data collection

The questionnaire will be uploaded to Porsline, a well-known online survey platform in Iran, to create a link for the questionnaire. Participants can use their mobile phones to open the link and fill out the questionnaire. A baseline assessment will be conducted prior to the intervention for both the intervention and control groups. In order to assess the immediate and long-term effects of the intervention prospectively, the first follow up assessment will be conducted immediately after the intervention, and the final one will be conducted 12 weeks later. Our primary outcomes are the number of mothers who have donated their breast milk and changes that have happened in breastfeeding mothers’ knowledge, attitudes, subjective norms, perceived behavioral control about DHM and intention to donate milk. Our secondary outcomes are the associations of behavioral determinants and social demographic variables with milk donation.

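### Control mothers come from only four of 20 centers although control centers host no classes; spreading them over eight would gain a little precision cheaply

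*Protocol article*

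**What the plan says.** All references are to the protocol article.

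- **Study design** makes this a cluster trial: "A cluster randomized controlled trial will be carried out on breastfeeding mothers referred to health centers". Its reasons for clustering are easier attendance at local classes, avoidance of contamination, and better representativeness.
- **Setting** gives the pool: "These four districts have a total of 20 health centers". Eight of these are drawn at random and divided equally between the arms: "a cluster of four centers will be randomly selected for collecting the intervention group and four centers for collecting the control group". On cluster size, it says: "We will recruit eight to nine participants from each health center".
- **Sample size** fixes the mothers: "we plan to recruit 33 samples per group and a total of 66 study participants".
- **Intervention design** shows where the classes are: "Sessions will be held in health centers for the intervention group while the control group will receive only usual education".
- **Data collection** uses an online questionnaire: "Participants can use their mobile phones to open the link and fill out the questionnaire".
- **Statistical analysis** names repeated-measures ANOVA, the Friedman test, chi-square or Fisher's exact test, and logistic regression. It names no center term.

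**The concern.** In a cluster trial the number of centers governs precision at least as much as the number of mothers. Four intervention centers is understandable, because each needs its own series of classes. That cost does not arise in the control arm, where mothers receive usual education and answer by phone. None of the three stated reasons for clustering requires the controls to come from four centers, and representativeness favors more.

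With four control centers of eight or nine mothers, one unusual center carries a quarter of the control mean, and a center-level comparison has 4 + 4 − 2 = 6 degrees of freedom. Twelve eligible centers (20 − 8) go unused. At stake is some precision that the same 66 mothers and the same four sets of classes could deliver. The number of centers is fixed by the design, so no later analysis plan can recover it.

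**Working it through.** **The plan's own figure.** The Sample size section uses SDs 3.21 and 3.17, a difference of 3, and z values 1.96 and 1.64:

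(1.96 + 1.64)² × (3.21² + 3.17²) / 3² = 12.96 × 20.353 / 9 = 29.3, rounded up to 30 per arm; 30 + 3 = 33.

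The article prints 29.4, which is what unrounded z values give. The figure reproduces. It is an individual-level formula with no term for centers.

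**Inputs for the comparison.** SD 3.19 (root mean square of 3.21 and 3.17), difference 3, and 30 analyzed per arm (33 less the attrition allowance). The ICC is an assumption, taken as 0.01, 0.05 and 0.10.

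**Standard error.** With n = 30 mothers in k centers, m = 30/k and

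Var(arm mean) = SD² × [1 + (m − 1) × ICC] / n.

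Four centers give m = 7.5; eight give m = 3.75. At ICC 0.05:

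- four centers: 10.176 × 1.325 / 30 = 0.4494
- eight centers: 10.176 × 1.1375 / 30 = 0.3858
- SE for 4 v 4: √(0.4494 + 0.4494) = 0.948
- SE for 4 v 8: √(0.4494 + 0.3858) = 0.914, which is 3.6% lower

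**Power.** For 4 v 4, the noncentral t formula on 6 degrees of freedom gives 83.5%, 75.1% and 65.9% at the three ICCs, and simulation agrees.

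For 4 v 8 the formula is optimistic. It gives 87.8%, 81.7% and 74.3% with Satterthwaite degrees of freedom, and 89.3%, 84.0% and 77.5% with 10 pooled degrees of freedom. Means of three or four mothers vary more than means of seven or eight, so the pooled formula does not describe the test that would be run. The tests on center means were therefore simulated directly:

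| ICC | SE, 4 v 4 | SE, 4 v 8 | Fall in SE | Power, 4 v 4 (pooled t) | Power, 4 v 8 (unequal variance) | Power, 4 v 8 (pooled t) |
|---|---|---|---|---|---|---|
| 0.01 | 0.850 | 0.842 | 0.9% | about 83% | about 86% | about 83% |
| 0.05 | 0.948 | 0.914 | 3.6% | about 75% | about 79% | about 78% |
| 0.10 | 1.058 | 0.996 | 5.9% | 65-66% | about 72% | about 72% |

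The pooled test is the natural comparator at 4 v 4, where the two arms' center means have the same variance. At 4 v 8 the unequal-variance test holds its type I error just under 5%. The pooled test on unweighted center means falls to about 3-4% and gains nothing at ICC 0.01.

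**Going further.** With all 16 remaining centers as controls, the SE at ICC 0.05 is 0.896 against 0.914 for eight, only 2% lower again. The four intervention centers become the limit.

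**The case against.** The strongest reply is that nothing here is misstated. Equal numbers of clusters per arm is a conventional and simple choice, and the gain is small and depends on an ICC nobody has given. Both parts stand, and they make this a suggestion rather than a fault.

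Four further points also stand:

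- **The analysis.** The named tests carry no center term, so under them the extra degrees of freedom would not show in the reported result. The design change needs an analysis change with it.
- **The endpoint.** The scale outcomes are defined as changes from baseline. Stable differences between centers cancel in a change score, so the relevant ICC may lie at the low end, where the gain is about two to three points of power.
- **Donation.** The number of mothers who donate is binary and is the main objective. No gain has been calculated for it.
- **The cost.** The Recruitment section has mothers approached by convenience sampling, giving written consent and completing the pretest. A phone link does not remove that work. Recruiting four or five mothers per control center against eight or nine per intervention center also makes convenience recruitment differ somewhat by arm.

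What the reply does not supply is a reason in the article for stopping at four control centers.

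A reader might infer that 4 v 4 leaves too few allocations for a valid test. It does not: there are C(8,4) = 70, and the smallest two-sided permutation p-value is 2/70 = 0.029, below 0.05.

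**Conclusion.** The point holds as a modest, avoidable inefficiency. The article has 20 centers, uses four for controls, holds no classes there, and gives no reason for the limit. Spreading the 33 controls over eight centers lowers the SE for any ICC above zero, by about 1% to 6% over ICC 0.01 to 0.10, and adds about 2 to 7 points of power. This rests on SD 3.19, a 3-point difference, 30 analyzed per arm, a single continuous score, an assumed ICC, and an unequal-variance test on center means.

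A reader might infer a larger benefit by counting 10 pooled degrees of freedom instead of 6. That would suggest gains of about 6 to 12 points, but the simulated tests do not reach them. Nor do the documents support calling the 4 v 4 layout an error or a contradiction, or claiming a calculated gain for every outcome. Severity: consider.

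**What to change.** In **Setting**, draw 12 of the 20 centers at random. Randomize four to intervention, with eight or nine mothers each as now, and eight to control, with four or five mothers each (33/8 = 4.1). The 66 mothers and the four sets of classes stay the same.

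In **Statistical analysis**, replace the tests that ignore centers with an analysis that respects them and allows for unequal numbers of centers per arm. For the scores, this could be an unequal-variance test on center means, or a mixed model with a random center effect and small-sample degrees of freedom. A pooled t-test on unweighted center means should be avoided, since it gives back much of the gain at low ICC. The donation outcome needs its own method that respects centers.

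The text changes are short. The practical cost is permissions, in-person recruitment and consent at four more centers of the same university, which the article does not cost, plus unequal cluster sizes between arms. Applying the same approach procedure in every center would limit the risk that recruitment differs by arm.

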### Recruitment

Eligibility for the study is as follows: being breastfeeding mothers who are within one year after giving birth and have sufficient breast milk for their own baby, with the approval of a doctor or midwife, having no serious medical condition (both mother and infant), and being a resident of Tehran.

The exclusion criteria are: breastfeeding cessation, loss of baby, not participating in more than one session of educational program, and not responding to more than 20% of the questionnaire.

Breastfeeding mothers who meet the inclusion criteria will be selected by convenience sampling, and they will be approached to explain the study aims, risks and benefits in a way that is easily understood. If they give permission to participate in study, they will provide written informed consent, then they will fill out the pretest questionnaire in order to obtain the baseline assessment.

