### Intervention design

Following baseline data collection, the intervention group will start receiving 60-minute weekly educational intervention based on TPB components for four weeks (Table 1).

**Table 1 Tab1:** The content of the educational sessions based on the theory of planned behavior

Session	Main purpose	Educational materials	Educational methods and time schedule
1	Improving breastfeeding mothers’ knowledge and attitudes toward DHM and HMB	• PowerPoint presentation • Booklet (including contents of all sessions) • Pamphlet of the first session	1) Introducing presenter and participants and explaining study aims (10 min) 2) Giving information on importance and background of breast milk donation and HMBs (40 min) 3) Question and answer (10 min)
2	Addressing the role of subjective norms in breast milk donation	• PowerPoint presentation • Pamphlet of the second session	1) Reviewing previous session (5 min) 2) Giving information related to Islamic laws of milk donation (15 min) 3) Presenter will use the psychodrama method. In this method two volunteer breastfeeding mothers role-play problems and release their intense emotions in regard to milk donation, then the presenter will guide their subjective norms [26] (30 min) 4) Question and answer (10 min)
3	Addressing the role of perceived behavioral control in breast milk donation behavior	• PowerPoint presentation • Pamphlet of the third session • Video	1) Reviewing previous session (5 min) 2) Giving information on requirements for breast milk donation, indication and contraindication of breast milk donation, process and cost of HMBs and current status of HMBs in Tehran (40 min) 3) Screening a video which shows how a HMB works (5 min) 4) Question and answer (10 min)
4	Addressing the behavioral intention and explaining how to implement the behavior of donating breast milk	• PowerPoint • Pamphlet of the fourth session • Video • Breast pump	1) Reviewing previous session (5 min) 2) Giving information on breast milk expression (10 min) 3) Showing how to express breast milk by hand and breast pump (25 min) 4) Showing videos of successful breast milk expression (10 min) 5) Question and answer (10 min)

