### Development of the measurement tool

Data will be measured by a 46-item researcher-made questionnaire. This instrument has been created by reviewing literature on milk donation and previous studies on TPB and consists of seven sections as described in Table 2.

**Table 2 Tab2:** Theory of planned behavior-based survey questions

Sections	Example of questions	Scale
Sociodemographic and perinatal characteristics	Age, education, milk and blood donation history, breastfeeding history, economic status, parity, mode of delivery, the gestational age, sex and age of infant, awareness of HMBs and the source of information of HMBs	-
Knowledge of DHM and HMBs	“What is a human milk bank?” “What is the best alternative to mothers’ own milk for feeding premature babies?” “What effects does pasteurization have on donor milk?” “In the hospital, which babies receive donor milk?” “Who is eligible to donate their breast milk?” “How is donor milk stored in the hospital?” “How long can donated breast milk be stored in the hospital?” “What effects has pasteurized donor milk on premature babies?” “What should mothers do before donating their breast milk?” “What are the characteristics of informal breast milk sharing in the community?”	Multiple-choice questions
Attitude toward DHM and HMBs	“It is pleasant for me to donate breast milk” “Feeding premature babies with donor milk is better than formula” “Donor milk can reduce the stress of mothers who can’t feed their babies with their own breast milk” “By donating breast milk to a milk bank, I can save a baby’s life” “Donating breast milk to the milk bank can reduce the incidence of serious gastrointestinal disease in infants” “Donor milk in milk banks is safe and healthy” “When I don’t have enough breast milk, it is better to use donor milk instead of formula to feed my baby” “Donor milk in a milk bank may carry viruses and spread disease” “Donor milk should be used widely in hospitalized infants who cannot be breastfed, if it is possible” “Donor milk can treat newborns who weigh less than normal” “I think mothers should be rewarded for donating their milk” “After pasteurization, the nutrients in milk are all destroyed, so it is better to feed baby with formula”	5-point Likert (from strongly agree to strongly disagree)

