Subjective norms about DHM and HMBs	“My husband’s opinion on donating milk to the milk bank is important to me” “I will not donate my breast milk to the milk bank if my husband disagrees” “Opinions of people around me like my mother, family, friends etc. on donating milk are important to me” “I will not donate my milk to the milk bank if people around me (like my mother, family, friends etc.) disagree” “Milk donation and using donor milk have ethical issues in Islam” “God considers milk donation as a virtue and admirable action” “If I want to donate my milk, my family will support me”	5-point Likert (from strongly agree to strongly disagree)
Perceived behavioral control in milk donation	“I feel donating my milk will decrease my milk supply which is needed for my own baby” “It costs me a lot to donate my milk” “I can provide equipment for milk donation such as a container for storing milk, breast pump (if needed)” “I think I can be a milk donor” “If my husband or family are against donating milk, I can convince them” “I can express my breast milk correctly” “I can provide storage conditions for expressed milk”	5-point Likert (from always to never)
Intention to donate milk	“I am going to donate my milk to a milk bank within the next six months” “I am going to identify the milk banks where I live” “I am going to contact a milk bank within the next six months” “I am going to identify the nearest route to the milk bank” “I am going to undergo a pre-donation blood test” “I am going to inform other breastfeeding mothers about milk banks” “I am going to provide equipment for milk donation”	5-point Likert (from always to never)
Breastmilk donation	“I donated my breast milk in the last six months” “How many times did you donate your milk to the milk bank in the last six months?” “I will follow hygiene tips if I want to donate my breast milk”	Yes / No Number 5-point Likert (from always to never)

Theory of planned behavior assumes that individuals’ behavior is directly determined by three main components, namely: attitude, subjective norms, and perceived behavioral control [18, 19].

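### Mothers who have already donated in this lactation can enrol, and the primary donation count does not require that donation starts after baseline

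*Protocol article*

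**What the plan says.** All references are to the Protocol article.

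- **Recruitment.** The inclusion criteria begin with "being breastfeeding mothers who are within one year after giving birth and have sufficient breast milk for their own baby" and go on to clinical approval, absence of serious illness in mother and infant, and residence in Tehran. The exclusions are "The exclusion criteria are: breastfeeding cessation, loss of baby, not participating in more than one session of educational program", plus leaving too much of the questionnaire unanswered. None concerns past or current milk donation. Mothers are chosen by convenience sampling.
- **Objectives and Hypothesis.** The main objective is to "assess the effectiveness of an educational intervention based on TPB in breastfeeding mothers on donating breast milk to HMBs". The hypothesis is a causal chain: education shifts knowledge, attitude, norms, perceived control and intention, and these then change behavior. The abstract's discussion asks whether the program can "lead to a significant increase in the number of potential milk donors".
- **Data collection.** "Our primary outcomes are the number of mothers who have donated their breast milk", together with changes in the questionnaire scores. Both arms are assessed at baseline, directly after the program, and 12 weeks after that.
- **Development of the measurement tool, Table 2.** The sociodemographic section records "Age, education, milk and blood donation history, breastfeeding history", among other items. The donation section includes the yes/no item "I donated my breast milk in the last six months".
- **Statistical analysis.** Qualitative variables are compared by chi-square or Fisher's exact test. Logistic regression is named for the effect of demographic variables on donation. The section does not say that mothers already donating at baseline are set aside or adjusted for in the comparison of arms.

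**The concern.** The hypothesis credits the program with changing behavior. A mother who was giving milk to a bank before she enrolled already shows that behavior, and her continuing to give cannot be attributed to the classes. The outcome is a head count of donors, so she scores the same as a mother who began because of the program. Baseline donation history is collected, but the article gives it no role in eligibility or in the outcome definition.

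This is separate from the reach of the six-month recall. Even if the item asked only about donation since baseline, a continuing donor would still answer yes. The six-month wording widens the group, because a mother who donated shortly before enrolment and then stopped would also be counted.

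At stake is the behavioral primary outcome. Existing donors shrink the contrast between arms if they are spread evenly, and move it up or down by chance if they are not. The outcome probably has few events, so each one carries weight.

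**Working it through.** **Inputs from the protocol.** 33 mothers per arm (Sample size); four centers per arm with eight to nine mothers each (Setting); "60-minute weekly educational intervention based on TPB components for four weeks" (Intervention design); final assessment 12 weeks after the first follow-up (Data collection); six-month recall (Table 2); chi-square or Fisher's exact test (Statistical analysis). The Background reports 81 donors in 2020 and 51 in 2021 at one Iranian milk bank. The protocol gives neither the share of existing donors nor an expected donation rate.

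**1. The plan's own figure.** (1.96 + 1.64)² × (3.21² + 3.17²) / 3² = 12.96 × 20.353 / 9 = 29.3. The article prints 29.4, which is what unrounded normal quantiles give. This rounds up to 30, and 30 + 3 = 33 per arm. The calculation concerns a difference of 3 points on a score, so it says nothing about the donation count.

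**2. Who is counted.** Six months is about 26 weeks. The first follow-up falls at about week 4, so the item reaches 26 − 4 = 22 weeks before baseline. The final one falls at about week 16, so it reaches 26 − 16 = 10 weeks before baseline. At both times it counts mothers who gave milk only before enrolment as well as those who continue. A mother whose only donation was earlier than the window, for example with a previous child, is not counted.

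**3. Effect of one existing donor.** 1/33 = 3.0 percentage points on her arm's proportion. Two in one arm and none in the other give 2/33 = 6.1 points.

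**4. Can that change a conclusion?** Two-sided Fisher tests at 33 per arm, with assumed counts:

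| Donors, arm A vs arm B | p |
|---|---|
| 2 vs 0 | 0.49 |
| 5 vs 0 | 0.053 |
| 6 vs 0 | 0.024 |
| 6 vs 1 | 0.105 |

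For x versus 0 the formula is p = 2 × C(33, x) / C(66, x). Two existing donors alone do not produce a significant difference. One added to the higher arm at 5 vs 0 crosses 0.05 downward. One added to the empty arm at 6 vs 0 crosses it upward. These tests treat mothers as independent.

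**5. How many to expect.** Let d be the share of existing donors (assumed). Expected number per arm = 33d; chance of at least one among 66 = 1 − (1 − d)^66. The last column is the chance of two or more in one arm and none in the other, 2 × P(0) × P(≥2), binomial with n = 33.

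| d | per arm | at least one of 66 | two or more vs none |
|---|---|---|---|
| 0.1% | 0.03 | 6.4% | 0.1% |
| 0.5% | 0.17 | 28.2% | 2.0% |
| 1% | 0.33 | 48.5% | 6.2% |
| 2% | 0.66 | 73.6% | 14.5% |

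**6. Dilution when the arms are balanced.** If p is the rate of new donation among the others, the observed rate is d + (1 − d)p, so the risk difference shrinks by the factor (1 − d). With assumed new-donor rates of 2% (control) and 25% (intervention), the difference is 23.0 points at d = 0, 22.8 at 1% and 22.5 at 2%. Fisher power at 33 per arm is 71%, 67% and 64% respectively.

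**The case against.** The strongest case against runs as follows. The main objective speaks of breastfeeding mothers in general and of donating to milk banks; it does not mention first-time donors. Table 2 also asks how often a mother donated, so sustained or more frequent giving is measured. The Study design section values representativeness. The documents point to few existing donors: 51 to 81 a year at one bank, two hospitals with banks in Tehran, and little information reaching mothers. Centers are selected and allocated at random. Baseline status is recorded, and adjusting for it could properly sit in an analysis plan that is not shown.

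Much of this stands. Broad eligibility is a defensible choice, the likely number is small, and absence of an adjustment from a journal article is not in itself a fault.

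A reader might go further and infer that one or two existing donors could create or hide the trial's result. The documents do not support that: 2 versus 0 gives p = 0.49, and only a result already at the boundary can be tipped. Nor do they show a systematic direction. Bank locations relative to the centers are not given, and imbalance between randomly allocated centers can favor either arm. That such mothers would start near the top of the intention or control scales is plausible, but no figure in the protocol bears on it.

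What the objection does not answer is the outcome definition, which the article does fix. The primary outcome is a head count of mothers, not a frequency. A head count cannot credit the program with donation that began before it, and it cannot separate keeping a donor from gaining one.

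**Conclusion.** The point holds as a gap in the outcome definition, with modest expected harm. Eligibility admits mothers who have already donated in the current lactation, and the primary count includes those who continue, or who gave within the recall window, regardless of arm.

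The size is 3.0 percentage points per such mother in her arm. With balance, the risk difference is multiplied by (1 − d), which is under half a point of loss at d = 1% (23.0 − 22.8 = 0.2 under the assumed rates). With imbalance, the estimate moves in an unpredictable direction, and the test result changes only near the boundary.

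All of this depends on a share that the documents do not give; shares of 0.1% to 2% are illustrations. The change is worth making because it costs almost nothing and brings the outcome into line with the stated hypothesis. It does not imply that the trial's conclusion would otherwise be wrong.

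**What to change.** Define the primary donation outcome as a first donation to a milk bank in the current lactation after baseline, among mothers with no milk-bank donation since the birth of the current infant. Either of two routes will do:

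1. an eligibility line to that effect, checked in the same way in both arms; or
2. enrolment as planned, with mothers who had donated by baseline left out of the analysis of this outcome only.

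Under either route, report baseline donation by arm. Mothers who donated only after an earlier birth can remain.

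The donation history is already in the baseline questionnaire, so no new instrument is needed. Its exact wording is not shown, so it should be confirmed that the item identifies donation since the current birth. The six-month item alone would miss earlier donation by a mother whose infant is older than six months. The first route also needs the question asked before enrolment, because the questionnaire is completed after consent.

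The cost is that a few mothers do not contribute to this outcome, and its conclusion applies only to mothers not yet donating.
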